**Statistical analysis**

Due to the fact that pigs will be clustered in households that are also clustered in villages and climates, a hierarchical logistic regression model will be used to analyse the data in order to take care of different levels of clustering and possible interactions. The effectiveness of intervention in improving human perceptions and practices will be computed by comparing average scores in the two groups adjusted for baseline values. Change in the prevalence of porcine cysticercosis will be computed and adjusted for important confounders such as age, sex of the pig, and other important household characteristics that might affect the prevalence of the disease. Seasonal prevalence of porcine cysticercosis will be taken into considerations when evaluating the intervention.

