The epidemiological cycle of *T. solium* occurs mostly in environments with low socio-economic or low hygiene levels, deficient sanitary facilities, or poor pig rearing practices where pigs can gain access to human faeces. Cysticercosis is most common in developing countries of Latin America, Asia, and Africa (Plancarte *et al.,* 1999). However, due to migration of people and tourism, human cysticercosis is now transmitted world-wide and it is considered as an emerging disease in the United States of America (Flisser *et al.,* 1998). Human cysticercosis has been reported in non pork-consuming communities such as the orthodox community in the USA (Schantz *et al.,* 1992). Studies on *T. solium* infections in Tanzania have largely been based on the infections in pigs, however, the possible medical implication of the parasite has been suggested by the presence of hospital records of human epilepsy and taeniosis in the studied areas ([name], 1999; Boa, unpublished report). A study conducted at household level in 21 randomly selected villages in Mbulu district northern Tanzania, established an overall prevalence of 17.4% (range 3.2-46.7%) of porcine cysticercosis in 770 live pigs examined by lingual examination ([name], 1999). This prevalence is higher than those reported by some similar studies in other highly endemic regions of the world. For example in Nigeria 5.5% of 1 300 pigs examined were found to be infected (Onah and Chiejina, 1995) while in Mexico, a prevalence of 4% was reported in 571 live pigs examined (Sarti *et al.,* 1992). Mbulu district was found to have a high potential for the spread of *T. solium* infections due to identified transmission factors. Out of 425 households observed, 21.6% did not have latrines. Of 198 respondents to interviews, 94.4% allowed their pigs to roam for food, and 41% of the respondents lacked knowledge on how a pig could acquire cysticercosis ([name], 1999). Thus, public health education could contribute in reducing the risk of this severe disease. Several studies have found that neither age nor sex of the pig had a significant association with the prevalence of porcine cysticercosis (Sarti *et al.*, 1992; Onah and Chiejina, 1995; Sakai *et al.*, 1998; [name], 1999). Studies in young pigs have indicated that infection rates are significantly higher in dry than in wet season (De-Aluja *et al.*, 1998; [name], in process). In the study in Mbulu, this was linked to the fact that during dry season pigs are let free to look for food in the fields since at this time crops have been harvested. On the other hand during wet season pigs are housed or tethered to restrict them from destroying crops in the fields. Seasonal prevalence of porcine cysticercosis should be considered when targeting and evaluating control measures.

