##### This will be a controlled randomised intervention trial with pre- and post-intervention examination of the study population. The pre-intervention study will be concerned with assessing the prevalence of porcine cysticercosis and its economic impact to the farmer. The study will also assess human perceptions and practices related to the transmission of *T. solium* infections in the area. Following the pre-intervention study, an intervention will be done in which participants in half of the selected villages will receive the health education while half of the villages will act as control. The village will be the unit of intervention allocation. Allocation of the villages to either intervention or control group will be done on a random manner or matched if randomisation will seem to favour communication between groups. Post-intervention study will be conducted to re-assess human perceptions and practices related to the disease, and the prevalence of porcine cysticercosis. The independent variables are therefore the prevalence of porcine cysticercosis, human perceptions and practices related to the disease, while the dependent variable will be the health education.

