**Study population**

Sample size calculation:

Although the village will be the unit of intervention allocation, the main analysis will be based on individuals since from previous study there was little variation in the prevalence of porcine cysticercosis in different villages (coefficient of variation was about 0.1). Therefore the sample size has been calculated using the formula,

n = [(z1 + z2)2 2P (1-P)]/(p1 – p2)2.

In the formula, n is number of pigs required in each group, z1 is the z score for the specified confidence level, and z2 is the z score for the specified power. p1 and p2 are the prevalence of the disease in the intervention and control group respectively, and p1 and p2 P is the average of p1 and p2 (Smith and Morrow, 1996).

The sample size is calculated based on the prevalence of porcine cysticercosis as the main outcome measure. The prevalence of porcine cysticercosis in the area was estimated to be 14.64% adjusted for various confounders ([name], 1999). We would like the present study to have 80% power to detect a significant difference with 95% confidence if the intervention will reduce the prevalence of porcine cysticercosis by 30%. The number of villages required in each group is therefore calculated to be:

n = [(1.96 + 0.84) 2 2 x 0.1244 (1-0.1244)]/(0.1464-0.1023)2

= 878.20.

Approximately 900 pigs will be examined in each of the two groups. A total of 1800 pigs will be examined before intervention and 1800 after intervention.

Selection of villages and study participants:

The number of villages to be included in the study will depend on the number of pig farmers available in the villages. This information will be obtained in the pilot study. All pig farmers in the selected villages will be enrolled in the study.

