**Study limitations**

Due to the short period available for the data collection (about two years), it might not be possible to observe significant reduction in the disease prevalence. However, improvement in perceptions and practices related to the transmission of the disease will be used as intermediate outcomes to indicate reduction in the transmission of the disease.

Maternal antibodies due against porcine cysticercosis have been reported to persist beyond nine months of pig’s life. This may limit the use of ELISA or immunoblot tests that have been reported to respond on these antibodies. This is because we would like to detect actual cases (and not false positives due to maternal antibodies) and to be able to disentangle cases hat occured before and those that occurred after the intervention. Most studies on antigen ELISA for porcine cysticercosis are still under trial and some have reported that antigens are detected up to 200 days post-infection and tend to disappear afterwards probably due to formation of immune complexes.

We are not sure that we will get enough pigs for post-intervention study since we don’t know how prolific are the pigs in the study area. From the previous study, one farmer in Mbulu had an average of 1.8 pigs. Our aim is to examine a different population of pigs in the post-intervention from the pre-intervention study. This is because in this particular disease we cannot know the onset of the infection, otherwise we could include the pre-intervention population that had not been infected in the post-intervention study.

Due to the fact that the intervention is information based, leaking of information from intervention to the control group might be a problem. However care will be taken to have a clear geographical separation of the groups. In addition, participants in the control group will be assured well in advance that they will receive the intervention after the study in order to minimise chances of them seeking information from the intervention group. The researcher will investigate if there is any leakage of information from the intervention to the control group, or if there is any change in hygiene policy during the study period in order to take care of these during data analysis. [In this point I am still thinking if we can use blinding which is known to reduce bias]

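### If both survey rounds are pooled, the clustering levels named for the change in pig prevalence leave village-to-village differences in change out of the standard error, so the false-positive rate can exceed 5%

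*Protocol*

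**What the plan says.** Four statements in the protocol bear on this point.

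- **Allocation (Phase three):** "The village will be the unit of intervention allocation".
- **Pigs (Study limitations):** "Our aim is to examine a different population of pigs in the post-intervention from the pre-intervention study". With the same villages in both rounds, the design is a pair of repeated cross-sections within randomised villages.
- **Model (Statistical analysis):** "pigs will be clustered in households that are also clustered in villages and climates, a hierarchical logistic regression model will be used". The sentence goes on to give the purpose: "in order to take care of different levels of clustering and possible interactions". The interactions are not named.
- **Outcome (Statistical analysis):** "Change in the prevalence of porcine cysticercosis will be computed and adjusted for important confounders such as age, sex of the pig". The section adds that "Seasonal prevalence of porcine cysticercosis will be taken into considerations when evaluating the intervention", without a method.

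The section does not say whether the two rounds are fitted in one model, or which term tests the intervention. The sample size section (Study population) leaves the number of villages open until the pilot study. It justifies analysis at the level of the individual by the small variation between villages ("coefficient of variation was about 0.1").

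**The concern.** For a change, the randomised unit is the village's change between rounds. In a pooled model of both rounds, the intervention effect on change is the arm-by-round term. A village effect that is the same in both rounds cancels from that term, as does any household or climate effect that is constant over time. What remains in the standard error is pig-level sampling. Such a model in effect assumes that, education apart, all villages change alike.

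The protocol gives reasons why they might not. The Introduction links infection in young pigs to season and roaming. The Study area section describes rainfall from under 400 mm to over 1200 mm within the district. The post-intervention section foresees possible changes in hygiene policy, and the limitations mention African swine fever.

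If villages do drift differently, chance differences in drift between the arms are read as an effect of the education. At stake is the type I error of the test of objective (iv), on the outcome that the sample size section treats as the main one. Having a village level in the model makes the analysis look protected, but that level handles clustering within a round, not differences in change between rounds.

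**Working it through.** **Plan's own figure.** n = (1.96 + 0.84)² × 2 × 0.1244 × 0.8756 / (0.1464 − 0.1023)² = 878.20 per group, rounded up to about 900. This reproduces.

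**Inputs from the protocol.** About 900 pigs per arm per round, prevalence 14.64%, coefficient of variation (CV) 0.1; earlier survey of 770 pigs in 21 villages, overall prevalence 17.4%, village range 3.2-46.7%.

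**Assumptions, not in the protocol.**
- 10 villages per arm of 90 pigs, or about 24 of 37 pigs (770/21 ≈ 37, the average in the earlier survey; 900/37 ≈ 24).
- Correlation c of a village's effect between rounds of 0.5 to 0.8.
- Equal village sizes. Household clustering is ignored.

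**Formula.** For m pigs per village per round and intraclass correlation (ICC) ρ, the arm-by-round contrast without a village-by-round effect has

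true variance / assumed variance = R = 1 + mρ(1 − c)/(1 − ρ),

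and the two-sided false-positive rate at nominal 5% is 2[1 − Φ(1.96/√R)].

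**ICC at the plan's CV.** ρ = (0.1 × 0.1464)² / (0.1464 × 0.8536) = 0.0017.

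**ICC suggested by the earlier survey.** The Introduction says that it "established an overall prevalence of 17.4% (range 3.2-46.7%) of porcine cysticercosis in 770 live pigs examined by lingual examination".
- Observed SD ≈ 43.5/3.78 = 11.5 points (3.78 is the expected range of 21 normal values in SD units).
- Binomial SD = √(0.174 × 0.826/36.7) = 6.3 points.
- Between-village SD ≈ √(11.5² − 6.3²) ≈ 9.7 points.
- CV ≈ 9.7/17.4 ≈ 0.55; ρ ≈ 0.097²/(0.174 × 0.826) ≈ 0.065.

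This is rough, so I use 0.05.

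**Results.**

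| ICC | Pigs per village (villages per arm) | c = 0.8: R, rate | c = 0.5: R, rate |
|---|---|---|---|
| 0.0017 (CV 0.1) | 37 (24) | 1.01, 5.1% | 1.03, 5.4% |
| 0.0017 (CV 0.1) | 90 (10) | 1.03, 5.4% | 1.08, 5.9% |
| 0.05 | 37 (24) | 1.39, 9.6% | 1.97, 16.3% |
| 0.05 | 90 (10) | 1.95, 16.0% | 3.37, 28.6% |

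At CV 0.1 with 10 villages per arm, even if all village variation were specific to a round (c = 0), the rate is 6.8%.

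**Simulation checks.**
- At ICC 0.05 and c = 0.8 (600 runs per setting), the rate was 10.2% with 37 pigs per village and 17.2% with 90. A t-test on village-level changes in log odds gave 5.3% and 5.2%.
- A separate set (4000 runs per setting) used CV 0.5 and 20 villages per arm. With 25%, 50% and 100% of village variance specific to a round, the rates were 10.8%, 16.2% and 25.4%.
- Across that second set (CV 0.1, 0.25 and 0.5; 10 and 20 villages per arm), a village-level test of change stayed at 4.3-5.7% and a village-level comparison of the post-intervention round alone at 4.2-5.7%. With no round-specific variance, the pooled analysis gave 4.6-5.5%.

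**The case against.** **The pooled model is not written down.** This is correct. The text is compatible with computing a change for each village. Because villages are grouped by baseline prevalence before randomisation, it is also compatible with comparing the post-intervention round alone with a village level. Both alternatives hold the error near 5%. The point is therefore conditional on pooling. Pooling remains a natural reading, because the protocol specifies a pig-level hierarchical logistic model and a change as the outcome.

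**The possible interactions might include village-by-round.** They might, and nothing excludes it. But none is named, and an arm or season interaction would not supply the missing variance. Nor would a fixed village-by-round interaction, which would absorb the arm-by-round effect. The term has to be a random effect.

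**Random-effects detail belongs in the statistical analysis plan.** Partly so. But this section already lists the levels and fixes the outcome as a change, and that combination is what leaves the gap.

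**The larger ICC is fragile.** It rests on two extremes and on equal village sizes. Neither extreme is possible with exactly 37 pigs (1/37 = 2.7%, 17/37 = 45.9%), so sizes varied, and small villages widen a range. This stands, and the ICC is only indicative. The stated CV is not firm reassurance either. At CV 0.1 the village SD is about 1.7 points, and adding binomial noise (6.3) gives about 6.5. The expected range over 21 villages is then 3.78 × 6.5 ≈ 25 points, against 43.5 reported.

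**Season may act alike everywhere.** A shift common to both arms cancels, and the plan does say that season will be considered. The protocol does not show that seasonal effects differ between villages; it only makes this plausible.

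**Conclusion.** The point holds as a conditional weakness. If both rounds are pooled with only the named levels, the test of the change in pig prevalence omits between-village variation in change. Its false-positive rate is then about 5-7% at the plan's CV of 0.1 with 10 or more villages per arm. It is about 10-29% with roughly 24 to 10 villages per arm if the ICC is near 0.05. The second range assumes a between-round correlation of 0.5 to 0.8, which the protocol does not give, and an ICC inferred roughly from the earlier survey's range.

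A reader might infer that the planned test is known to exceed 5%. The protocol does not support that: it fixes no pooled model, does not exclude a village-by-round term, and gives no round-specific variance. If villages do not drift differently, there is no excess. Fewer and larger villages would raise the figures, but the number of villages is left open, so I draw no conclusion from such cases.

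This concerns type I error and is separate from whether 900 pigs per arm give enough power.

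**What to change.** Add one sentence to the Statistical analysis section: if both rounds are analysed together, the hierarchical logistic model includes a village-by-survey-round random effect, so that the arm-by-round effect is tested against between-village variation in change. With few villages, compute each village's change (log odds, post minus pre) and compare the arms with a t-test whose degrees of freedom come from the number of villages. The same sentence should say which term tests the intervention.

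No extra data are needed. The cost is a wider confidence interval for the intervention effect: slight if villages change alike, larger if they do not.

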##### Study area

Mbulu District is located in north-eastern Tanzania, between latitude 3.80o-4.50oS and longitude 35.00o-36.00oE. The altitude varies from 1000-2400 m above sea level. The area has a semi-arid and sub-humid climate and receives an annual rainfall of less than 400 mm and over 1200 mm respectively. The long rainy season extends from about March to Mid-May and the short rainy period extends from November to December. Relative humidity ranges from 55%-75% and mean annual temperature ranges from 15oC-24oC. The District has 59 villages and the 1997 District census showed that it had a population of 200 000 people and 32 883 pigs. Crop and livestock production is by far the most important economic activity, employing over 90% of the total District labour force. Most of the inhabitants are Iraqw tribe that occupies most of the highland areas and practices mixed farming. Pigs are raised in most households as a source of income and animal protein for the household. Most of the pigs are let free to graze particularly after harvesting. When there are crops in the fields most pigs are tethered at the backyard and are fed on cut grass, kitchen leftovers, pumpkins and maize grains. Few farmers house their pigs. Slaughtering of pigs takes place at home although few of the pigs are slaughtered at a nearby open slaughter slab. Some home slaughtered pigs are inspected by a meat inspector while some are not. Besides pig farming, villagers also raise other livestock including cattle, sheep, goats, and chicken. Some villagers keep dogs, cats, as well as donkeys.

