# Allocation of villages to intervention:

Two groups will be compared whereby one group will receive the health education while the other group will act as a control. The villages will be grouped according to their similarities in their prevalence of porcine cysticercosis obtained during pre-intervention study and randomised within groups to either control or intervention.

Intervention:

Participants in the control group will follow their usual hygiene and pig management practices. For the intervention group, the educator in each village will organise and conduct two training sessions one- month interval. After the first session the educator will distribute pamphlets to the participants for further reference. The day after the session, the participants in the intervention group will watch a video program. The researcher will participate in the sessions as an audience, therefore the interventions in the selected villages will be planned such that the researcher will participate in all the villages.

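### Climate is listed as a clustering level although only two climates are described; the model statement should make it a fixed two-category covariate

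*Protocol*

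**What the plan says.** The Statistical analysis section of the protocol states that "pigs will be clustered in households that are also clustered in villages and climates". It follows that "a hierarchical logistic regression model will be used to analyse the data in order to take care of different levels of clustering". Climate therefore stands in the same list as household and village. The section does not say which levels are random and which are fixed. The change in prevalence is to be "adjusted for important confounders such as age, sex of the pig, and other important household characteristics"; this list is open-ended and does not name climate.

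The Study area section states: "The area has a semi-arid and sub-humid climate". It gives a separate rainfall figure for each of the two, so the natural reading is two zones.

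On allocation, "The village will be the unit of intervention allocation". Under Allocation of villages to intervention, "The villages will be grouped according to their similarities in their prevalence of porcine cysticercosis", and villages are randomised within those groups. Climate is not a grouping factor. The number of villages is open: "The number of villages to be included in the study will depend on the number of pig farmers available in the villages".

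**The concern.** A random level describes a population of units from which those in the study are a sample. Many households and a moderate number of villages can support that; two climates cannot. In a random-intercept model the estimated climate variance decides how far the climate difference is taken out of the arm comparison. If the variance is estimated as zero, nothing is taken out. If it is small, only part is.

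Climate is not an allocation factor, so the arms can differ in climate by chance. If prevalence also differs by climate, part of that difference could remain in the estimated effect of the education. The reader of the results would believe that climate had been handled.

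**Working it through.** **1. The yardstick.** The plan's sample size uses 14.64% against 10.23%, with P = 0.1244:

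(1.96 + 0.84)² × 2 × 0.1244 × 0.8756 / (0.1464 - 0.1023)² = 7.84 × 0.21785 / 0.00194481 = 878.20, as printed.

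The same two prevalences give a planned log odds ratio of ln[(0.1023/0.8977)/(0.1464/0.8536)] = ln(0.664) = -0.409.

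**2. Precision of a variance from two units.** With g units there are g - 1 degrees of freedom. Even if the two climate means were known without error, the 95% limits for the variance, as multiples of the estimate, are 1/5.024 = 0.20 and 1/0.000982 = 1018. On the standard deviation scale the limits differ by a factor of √(1018.26/0.19905) = 72. With 20 units the factor is 1.9.

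**3. Chance of imbalance.** Assume half the villages lie in each climate and simple randomisation is used. The chance that the arms differ by at least 40 percentage points in climate share is 21% with 10 villages (52 of 252 allocations), 18% with 20, and 3% with 30 or 40. Grouping on baseline prevalence lowers this if climate drives prevalence.

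**4. What the random level leaves behind.** Village-level simulation, post-intervention data only, 500 runs per setting. All inputs are assumed except the total of 1800 pigs and the average prevalence of 0.1244: residual village SD 0.3 on the logit scale, no intervention effect, REML, and the imbalance imposed. Entries are mean bias in the log odds ratio.

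| Villages | Climate OR | Semi-arid villages, arm 1 v arm 2 | Variance estimated as 0 | No climate term | Random level | Fixed term | Random minus fixed |
|---|---|---|---|---|---|---|---|
| 10 | 1.5 | 4 v 1 | 32% | 0.253 | 0.087 | 0.004 | 0.083 |
| 10 | 1.5 | 3 v 2 | 26% | 0.074 | 0.016 | -0.008 | 0.024 |
| 10 | 2.0 | 4 v 1 | 10% | 0.394 | 0.050 | -0.028 | 0.078 |
| 10 | 2.0 | 3 v 2 | 4% | 0.129 | 0.009 | -0.009 | 0.018 |
| 20 | 1.5 | 7 v 3 | 16% | 0.160 | 0.035 | -0.008 | 0.043 |
| 20 | 1.5 | 6 v 4 | 14% | 0.087 | 0.022 | 0.002 | 0.020 |
| 20 | 2.0 | 7 v 3 | 1% | 0.275 | 0.029 | -0.003 | 0.032 |
| 20 | 2.0 | 6 v 4 | 0% | 0.135 | 0.007 | -0.006 | 0.013 |

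The column without a climate term agrees with theory: bias = ln(OR) × difference in climate share, for example 0.405 × (0.8 - 0.2) = 0.243 in the first row. The random level removes between 1 - 0.087/0.253 = 66% and 1 - 0.007/0.135 = 95% of it. The excess over the fixed term is 0.013 to 0.083, or 3% to 20% of 0.409. In runs with a zero variance, roughly the whole unadjusted bias remained. With no climate effect (OR 1.0) the variance was zero in 63% to 69% of runs, harmlessly.

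A separate simulation with its own assumed inputs gave zero variance in about 9% to 36% of runs and an excess of about 0.03 to 0.08.

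**5. Analysis of change.** Let the climate log odds ratio be d0 before and d1 after the intervention, and let s be the difference between arms in climate share. The climate contribution to the difference in change is (d1 - d0) × s, which is zero when d1 = d0. The separate simulation also found bias of about zero for change. Only a climate effect that shifts between surveys remains. As an illustration, a shift from OR 1.5 to 2.0 with s = 0.4 leaves (0.693 - 0.405) × 0.4 = 0.115 if nothing adjusts for it.

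**The case against.** The strongest reply is that the protocol never calls climate a random effect. A fixed climate factor with random households and villages would fit the wording, and this detail is often left to a statistical analysis plan, which is not at hand. That stands as far as it goes: the protocol does not commit to the weaker model. But it does name climate as a clustering level beside two that are ordinarily random, and does not name it among the confounders. The ordinary reading is the less suitable one, and the wording is worth settling.

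The second reply is that the design already limits the damage. Prevalence is compared as a change from baseline, and villages are grouped on baseline prevalence before randomisation. Both points stand and are the main reason the effect is likely small. They do not cover a climate effect that differs between the two surveys.

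The third reply concerns size. The sample size section gives a between-village coefficient of variation of about 0.1, which is a village SD of 0.01464/(0.1464 × 0.8536) = 0.12 logits. Two equally common climates with odds ratio 1.5 alone imply 0.405/2 = 0.20. On that figure the simulated climate effects are too large. The Introduction, however, reports village prevalences from 3.2% to 46.7%, which suggests more variation. The documents do not settle this, and none of them reports prevalence by climate.

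A reader might also infer from the Study limitations section, where "care will be taken to have a clear geographical separation of the groups", that the arms will lie in different climates. The text does not support this. The separation is meant to limit leakage of information, and nothing says that it follows the climate boundary.

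**Conclusion.** The point holds as a minor one. Two climates are too few to serve as a random level: the variance would rest on one degree of freedom, would be unreliable and would often be zero. A chance climate imbalance could then be removed only in part from a post-intervention comparison. Under the assumed settings the excess bias over a fixed term is about 0.01 to 0.08 in the log odds ratio, conditional on an unfavourable allocation, and close to zero for change if the climate effect is stable over time. These figures rest on assumed village numbers, climate split, climate effect and village SD. They show direction and rough scale and do not predict the bias of the planned analysis.

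It would go too far to say that the climate variance cannot be estimated at all, or that the model fails to adjust for climate. The variance can be computed, and on average the random level removed about two thirds or more of the imbalance.

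**What to change.** In the Statistical analysis section, state that climate (semi-arid or sub-humid) enters the arm comparisons as a fixed two-category covariate, with a climate-by-period term where change in prevalence is analysed, and that household and village are the random levels.

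The cost is one degree of freedom, or two with the climate-by-period term, taken at village level. With 10 villages (assumed), for example, a post-intervention comparison would have 10 - 3 = 7 residual village degrees of freedom instead of 10 - 2 = 8. The sample size calculation is unaffected and no extra fieldwork is needed beyond recording each village's climate zone.

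### Villages are randomised, but the comparison of perception and practice scores states no village level; if villages are ignored, the precision for objective (iii) would be overstated

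*Protocol*

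**What the plan says.** Under Phase three the protocol fixes the design: "The village will be the unit of intervention allocation". The Allocation section adds that villages are first grouped by similar pre-intervention prevalence of porcine cysticercosis and then randomised within those groups.

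The Statistical analysis section opens with the reason for a clustered model, which is that "pigs will be clustered in households that are also clustered in villages and climates". It continues that "a hierarchical logistic regression model will be used to analyse the data in order to take care of different levels of clustering". The next sentence gives perceptions and practices a method of their own: the effect will be "computed by comparing average scores in the two groups adjusted for baseline values". That sentence mentions neither village nor household.

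The sample size section says that "the main analysis will be based on individuals since from previous study there was little variation" in prevalence between villages ("coefficient of variation was about 0.1"). This figure is for infection in pigs. No between-village figure is given for scores.

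Study limitations concedes that a fall in prevalence may not be seen in the time available. It then says that improvement in perceptions and practices "will be used as intermediate outcomes to indicate reduction in the transmission of the disease".

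**The concern.** When villages are allocated, the information about an intervention effect lies largely between villages. Households in one village share surroundings and local habits. In the intervention arm they also share a teacher, since "the educator in each village will organise and conduct two training sessions". Their scores can therefore be expected to be correlated, and a comparison that counts each household as an independent observation would give standard errors that are too small.

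Specific objective (iii), the effect of the materials on perceptions and practices, rests on this comparison. The protocol also expects that these scores may have to carry weight if prevalence does not move, so their precision matters more than it would for an ordinary secondary outcome.

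What the scores may be taken to show is a second and separate question. A correct standard error would not turn a score into a measure of infection.

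**Working it through.** **The plan's own figure.** The only sample size is for pig prevalence: n = (1.96 + 0.84)² × 2 × 0.1244 × (1 − 0.1244) / (0.1464 − 0.1023)² = 878.20 per group, rounded to about 900. It reproduces exactly. It contains no design effect, and no corresponding figure exists for the scores.

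**Inputs from the protocol**
- Unit of allocation: village (Phase three).
- About 900 pigs per group (sample size section) and 1.8 pigs per farmer (Study limitations), so 900 / 1.8 = 500 farmers per group.
- All pig farmers in selected villages are enrolled, and practices are observed in all selected households (selection and data collection sections).
- Perceptions are studied by in-depth interviews of five farmers per village (data collection section).
- The number of villages is not fixed; the district has 59.

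**Assumptions.** ICC of 0.02 to 0.10; 20 to 50 households per village (500/20 = 25 to 500/50 = 10 villages per group); equal village sizes; normal reference distribution.

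**Formulas.** Design effect DE = 1 + (m − 1) × ICC, where m is the number of respondents per village. True two-sided error of a nominal 5% test that ignores villages = 2 × [1 − Φ(1.96/√DE)].

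| m | ICC | DE | True error |
| --- | --- | --- | --- |
| 5 | 0.02 | 1.08 | 5.9% |
| 5 | 0.05 | 1.20 | 7.4% |
| 5 | 0.10 | 1.40 | 9.8% |
| 20 | 0.02 | 1.38 | 9.5% |
| 20 | 0.05 | 1.95 | 16% |
| 20 | 0.10 | 2.90 | 25% |
| 50 | 0.02 | 1.98 | 16% |
| 50 | 0.05 | 3.45 | 29% |
| 50 | 0.10 | 5.90 | 42% |

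**If only the intervention arm is correlated.** The shared educator exists only there. If that were the sole source of correlation, with equal arms and equal variances, the variance of the difference would be inflated by (DE + 1)/2. For m = 20 and ICC 0.02 this is (1.38 + 1)/2 = 1.19, an error of 7%. For m = 50 and ICC 0.10 it is (5.90 + 1)/2 = 3.45, an error of 29%.

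**Are 20 to 50 households plausible?** The Study area section gives 32 883 pigs in 59 villages, about 557 per village, or 557/1.8 ≈ 310 farmers. Full enrolment of an average village would then exceed the range used. At m = 310 and ICC 0.01, DE = 4.09 and the error is 33%. This is a district average, so I use it only to show that 20 to 50 is not an extreme choice.

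**The case against.** The strongest reply is that the absence of a village level is inferred from silence. The section's opening sentence applies the hierarchical model to the data as a whole. The later sentence on prevalence also names no cluster term, yet the opening sentence plainly covers it. The score sentence specifies no test, standard error or unit of analysis, and an analysis plan could supply them. Some practices can be recorded as yes or no, for which a logistic model would serve. A reader might therefore go too far in inferring that the plan makes no allowance for villages and that significance will be overstated. The documents support neither statement in that absolute form.

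This limits the claim without removing it. An average score is not a logistic outcome, the stated reason for the model is pigs, and the scores have been given a different method. The sample size section also leans towards individual-level analysis, on a coefficient of variation that says nothing about scores.

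Three further objections stand in part. Shared sessions occur only in the intervention arm. Perceptions may be scored from only five farmers per village, where the inflation is small. Baseline adjustment would normally remove some stable between-village variation, so the relevant ICC is that of the adjusted score.

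On transmission, a reader might infer that a null prevalence result will be presented as success. The protocol does not say so. It keeps objectives (iii) and (iv) apart, names prevalence as the main outcome measure, and calls the scores intermediate outcomes. Practices such as pig rearing and latrine use are observed transmission factors and not merely recall of what was taught. What remains is wording that lets scores indicate reduced transmission.

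**Conclusion.** The point holds in conditional form. The protocol gives the perception and practice scores a method with no stated village level, and its clustering model is written for another outcome. If the analysis follows that text and ignores villages, the true error would be about 10% to 42% for household data with 20 to 50 households per village, and about 6% to 10% for a score from the five in-depth interviews, both for an ICC of 0.02 to 0.10. The figures depend on the assumed ICC, village size and equal correlation in both arms. They show a plausible size and do not predict the error of this trial.

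The inference from scores to transmission is a separate, smaller point. It calls for a limit on the conclusion and does not count against measuring these outcomes.

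**What to change.** In Statistical analysis, state that each score is analysed with a linear mixed model: follow-up score on arm, baseline score and the prevalence-based randomisation group, with a random village effect and small-sample degrees of freedom. Comparing baseline-adjusted village mean scores is an acceptable and simpler alternative.

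In Study limitations, say that perceptions and practices are reported as intermediate outcomes for objective (iii), and that a conclusion of reduced transmission rests on the prevalence of porcine cysticercosis.

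The cost is a few sentences and slightly more analysis; no new data are needed. Confidence intervals for the scores will be wider, markedly so if few villages are enrolled.
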